### Procedure

Primary healthcare centers from the province of Concepcion, Chile will be invited to participate. The participation of each center is approved by the Ethical-Scientific Committee of each health service and authorized by their directors. A requirement for the inclusion of a center in the study is the authorization for the participation of health workers in the program sessions during work hours. Various activities will be performed to promote the program in each selected health center and to encourage participation. The program will be implemented in health centers where there are at least 18 people enrolled to permit the randomization of control and experimental groups with at least nine people per group. Given the sizes of the centers, a maximum number of 40 participants will be considered per health center since it is unlikely that there will be more than that number of people enrolled. The randomization process will form groups with 9 to 20 people. All healthcare workers will be invited to participate through informative meetings and flyers distributed in each health center. Once the participants have agreed to take part in the program and have been evaluated, they will be randomized. The initial evaluation (T1) will take 3 weeks, and the implementation of the program will last a total of 8 weeks. The post-test evaluation (T2) will be done during the 3 weeks following the end of the program. Four months after the end of the program, the follow-up evaluation will be performed (T3) (Table 1).

**Table 1 T1:** Study assessment points.

**Measurement**	**Scale**	**T1**	**T2**	**T3**
**SOCIODEMOGRAPHIC DATA**				
Sociodemographic data	Sociodemographic characterization file	✔	–	–
**STIGMA IN PRIMARY HEALTHCARE WORKERS TOWARD PEOPLE WITH DIAGNOSIS OF SEVERE MENTAL DISORDERS (SMD)**				
Attitudes of the general public toward people with SMD	Community Attitudes to Mental Illness (CAMI) scale	✔	✔	✔
Attitudes of professionals and students working in health toward people with SMD	Mental Illness: Clinicians' Attitudes (MICA) scale	✔	✔	✔
Social distance that people have toward people with SMD	Social distance scale (SD)	✔	✔	✔
Self-perception of behaviors that one had toward the last person diagnosed with SMD with whom they had contact	Self-registration of inclusive behaviors	✔	✔	✔

*T1, assessment before intervention; T2, assessment after intervention; T3, follow-up 4 months after assessment T2*.

Workers assigned to the control group will receive the program once the implementation is completed and the post and follow-up evaluations are finished. A minimum of 11 centers are needed to obtain the required sample size (Table 1).

### Power and Data Analyses

An experimental multilevel mixed effects design with effects between groups (treatment vs. control) and within groups (time), with pre- and post-test measurements and with a four-month follow-up, will be used. Estimation of the effect will be by intention-to-treat. To estimate the effect of the intervention on post-test measurements, it should be taken into account that there are multiple outcomes and the results per person are not independent of each other but can have distinct distributions. Therefore, a multivariate analysis of covariance (MANCOVA) will be used where the presence of clustering per healthcare center is considered as a factor, while the pre-test measurement and previous contact with someone with SMD are considered as co-variables. Previous verification of the assumptions that the model provides, i.e., presence of normal multivariate distribution of the transformation of the measurements, as well as homogeneity of the variance/covariance matrix between the groups under study, is necessary.

Once it has been determined that the intervention is successful in general terms, specific analyses of each result will be performed using mixed ANCOVA that considers participation in the control group or experimental group as a fixed factor of interest, pre-measurement as a co-variable, and enrollment in the primary healthcare center as a random factor. To detect a moderate effect for the intervention (*d* = 0.5) with a power of 95% and a level of significance of 5%, a minimum sample of 105 participants per group is estimated (210 participants in total). This number was obtained by performing a simulation procedure using a mixed ANOVA considering the existence of a significant interaction effect between moment X group experimental/control. Considering a 10% loss in percentage, 231 is the minimum estimated number of participants.

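### No model named in the analysis section tests the four-month follow-up effect that both hypotheses claim, and the joint post-test MANCOVA fits poorly with the intention-to-treat aim

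*Protocol article*

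**What the plan says.** **Hypotheses** (protocol article, end of Introduction). Both compare the arms at the post-test evaluation and at follow-up: one on attitudes and social distance, the other on inclusive behaviours.

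**Data collection** (Procedure and Table 1). All four scales are completed at T1, T2 and T3. Controls receive the program only after the follow-up evaluation.

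**Analysis** (Power and Data Analyses). The design is described as multilevel mixed effects, with group and time effects and a four-month follow-up. "Estimation of the effect will be by intention-to-treat". Then:

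- The MANCOVA is introduced by "To estimate the effect of the intervention on post-test measurements". Centre is a factor; the pre-test measurement and previous contact are covariates.
- Once overall success is established, each result is analysed by mixed ANCOVA with group fixed, pre-measurement as covariate and centre random.
- For the sample size: "This number was obtained by performing a simulation procedure using a mixed ANOVA", on the assumption of a significant time-by-group interaction. The result is 105 per group, 210 in total, raised to 231 for 10% loss.

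**Timing of T3.** The Procedure section says "Four months after the end of the program, the follow-up evaluation will be performed (T3"; the Table 1 footnote says "follow-up 4 months after assessment T2".

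**The concern.** The hypotheses, the declared design and the sample size all involve change over time, and the hypotheses explicitly include follow-up. The named models do not. As controls are still untreated at T3, the follow-up is a full randomised comparison. The Introduction itself notes that changes after education alone are of limited duration, so persistence of effect is a main question. If the plan does not fix how T3 is tested, the choice is left until data are in hand. If the T3 analysis also waits on a post-test result, an effect seen mainly at follow-up might never be formally tested.

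A second issue is who enters the joint test. A standard MANCOVA needs every outcome and covariate for each worker. The inclusive-behaviours scale asks about the last person with a severe mental disorder whom the worker met, so a worker with no such contact may have no valid answer. By default that worker would leave the joint test of all four scales. The Introduction reports that contact is related to attitudes, so loss of this kind could plausibly be selective.

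**Working it through.** **1. Which element covers which time point**

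| Element | T2 | T3 | Time or group-by-time term |
|---|---|---|---|
| Both hypotheses | yes | yes | – |
| Declared design | yes | yes | yes |
| Sample-size model | not stated which occasions | not stated | yes |
| MANCOVA | yes | not mentioned | no |
| Mixed ANCOVA per outcome | not stated | not stated | no |

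The first three rows rest on time or on follow-up. The two models that are to produce the results have no time term, and neither is assigned to T3. As listed, the mixed ANCOVA also has no person effect, so it could not take T2 and T3 from the same worker together. Read in order, it depends on the post-test MANCOVA.

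**2. The plan's own sample size**

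Inputs from the plan: d = 0.5, power 95%, significance level 5% (taken as two-sided; one-sided gives 87 per group and does not fit).

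- Normal approximation: n = 2(1.96 + 1.645)² / 0.5² = 103.96, so 104 per group.
- Exact two-sample t-test: 105 per group, power 0.950.
- Simulated mixed ANOVA interaction, two occasions, 105 per group: power 0.950 if the pre-post correlation is 0.5 (assumed; the article gives none).
- 210 × 1.10 = 231.

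The stated figure reproduces; this point does not turn on a wrong number.

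**3. Would 210 support a group-by-time model with T2 and T3?**

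Simulated mixed ANOVA with three occasions, d = 0.5 at both T2 and T3, 105 per group, no centre effect:

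| Assumed correlation | 0.3 | 0.5 | 0.6 | 0.7 |
|---|---|---|---|---|
| Power | 0.90 | 0.97 | 0.99 | >0.99 |

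**4. Size of the possible complete-case loss**

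Planned loss only: 231 × 0.90 = 207.9, about 208 workers; two-sample t power 0.948.

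Illustration with additional missingness q on each of four post-test scales, independent across scales. Both q and independence are assumptions. Complete workers = 231 × 0.90 × (1 − q)⁴.

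| q | Complete workers | Power, unadjusted t-test, d = 0.5 |
|---|---|---|
| 2% | 207.9 × 0.922 = 192 | 0.93 |
| 5% | 207.9 × 0.815 = 169 | 0.90 |
| 10% | 207.9 × 0.656 = 136 | 0.83 |

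These powers ignore the pre-test covariate. With a pre-post correlation of 0.5 (assumed), ANCOVA needs 104 × (1 − 0.5²) = 78 per group for 95% power. At q = 5% about 84 to 85 per group remain, still enough; at q = 10% about 68 remain, which is not.

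**5. T3 timing**

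T2 is spread over the 3 weeks after the program ends. Four months from program end and four months from T2 can therefore differ by up to 3 weeks.

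**The case against.** A reader might go further and infer that the plan analyses only workers with complete data and so contradicts its intention-to-treat statement. The article does not say that incomplete workers are excluded. Dropping them is the default behaviour of a standard MANCOVA; imputation beforehand would be compatible with intention-to-treat, and missing-data handling may be set out in a fuller protocol or SAP that is not shown. What stands is a tension between method and aim.

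A reader might also infer a serious loss of power, or informative missingness built into the design. Neither is supported. The article gives no rate of scale-level missingness. Scales given at one visit tend to be missing together, which the 10% loss already covers, so the independence assumption overstates the exclusions. The pre-test is taken before randomisation, so baseline loss should be small, and a missed T3 visit removes nobody from a post-test MANCOVA. The single-outcome models can also use each worker who has that scale.

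On the models, an ANCOVA at one time point needs no time term or person effect, and separate ANCOVAs at T2 and T3 would be valid. With two occasions, the interaction and the baseline-adjusted difference target the same effect, so sizing on the interaction is not an error in itself. The declared design does include follow-up, and analysis of each result could be read to include T3, so calling the follow-up wholly unaddressed would be too strong. Even on that generous reading, the article does not assign a model to T3, and the step still waits on an overall success judged at post-test.

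**Conclusion.** The point holds as a mismatch inside the article. Follow-up is part of both hypotheses and of the declared design, and the trial is sized on a time-by-group interaction, yet no named model tests the follow-up effect, and the single-outcome step depends on a post-test result. This is more than detail left to a SAP, because the article does name its models and their terms.

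The intention-to-treat issue is secondary. It rests on standard MANCOVA behaviour, and its size cannot be known from the document. On the plan's own 10% loss power stays about 0.95, so the case rests on the missing T3 test and on possible selective loss, not on power. The T3 timing difference is a minor wording matter of at most 3 weeks.

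**What to change.** - For each scale, fit one linear mixed model to all randomised workers with any post-baseline outcome. Use T2 and T3 as responses with T1 as covariate, or include T1 as a response with the arms' baseline means constrained equal. Include group, time and group-by-time, with random person and centre effects.
- Report the group contrast at T2 and at T3, and do not make the T3 test depend on the post-test MANCOVA.
- State one anchor for T3, the same in the Procedure section and the Table 1 footnote.

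This brings the analysis into line with the hypotheses, the declared design and the basis of the sample size, and it keeps workers who have only some of the outcomes. The cost is revised analysis wording and slightly more analysis work in standard software, with no extra data. The results would rest on a missing-at-random assumption, which should be stated.

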In health care, several studies indicated that healthcare personnel have prejudices, negative attitudes, and discriminatory behavior toward people with SMD (16, 23–25). For instance, a recent study comparing professionals at both PHS and secondary healthcare centers found that physicians and nurses at PHS had more negative attitudes toward people with SMD than their colleagues at secondary healthcare centers (26). Although stigma is similar in different professional groups such as nurses (27, 28), physicians (29), pharmacists (30), and psychologists (31), there seems to be some differences between them. For example, professionals closest to the area of social sciences, such as psychologists, would have less stigma than professionals in the area of healthcare, such as physicians and nurses (32). Despite the few studies on this topic in Chile, the results are in agreement with other published studies demonstrating that there are prejudices and negative attitudes toward people who have SMD (33, 34). It has been shown that stigma affects the inequity of health care in several ways. For instance, there is abundant evidence describing the effect of barriers to access healthcare services that makes it difficult for the affected people to request help (35, 36). In Chile, the lack of knowledge about mental disorders and stigma are the main reasons Chileans do not seek treatment (37). On the other hand, healthcare personnel mistakenly attribute physical signs and symptoms to a mental disorder, which leads to sub-diagnosis and inadequate treatment of physical health problems (16). Finally, a negative attitude toward the patient is associated with a lower adherence to treatment. Therefore, healthcare personnel should be considered a priority group for anti-stigma interventions, especially those working in PHS (38).

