The other major strategy, contact with affected people, is limited to interventions in which a person with a mental disorder tells their experience to a specific group, either directly or indirectly through audiovisual media (48, 51). The conditions under which contact occurs are important for success. For example, the interaction should be cooperative, perceiving similar status, and not competitive. Indeed, the largest meta-analysis performed on the subject, which included 515 studies, determined that the conditions of contact raised by Allport contributed to diminishing prejudice; however, even if all conditions are not met, contact has a positive effect on decreasing stigma (52). For contact to be effective, it is important that people do not have behaviors and attitudes that are stereotypical of the SMD, and that they have the support of the directors of the Center where the intervention is carried out. Contact seems to be the best strategy to reduce stigma against people with SMD. In fact, several studies indicate that subjects who interact with people who have SMD are less likely to have negative attitudes toward them (53, 54). In a study performed in Chile on the perception that the general public and healthcare workers have toward people with SMD, it was found that those who had greater contact with people with SMD had less authoritarian and restrictive attitudes (55). Indeed, studies performed with healthcare personnel demonstrate that using direct contact with people with SMD is a strategy that decreases negative attitudes and social distance and increases acceptance toward this social group (23, 56, 57). However, the main limitation to developing this strategy is that it requires that people affected by a mental disorder be willing to publicly disclose their condition and talk about it. Despite this difficulty, studies suggest that the active involvement of those affected in these interventions increases their self-esteem and empowerment, which are fundamental for their recovery (54).

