## Methods

### Design

The study design is a multicenter randomized clinical trial in which several primary healthcare centers in the province of Concepcion, Chile will participate. Randomization will be at the individual level (Figure 1). The randomization will be performed by blocks (each healthcare center will be a block) and will be performed after identification of all the people who have agreed to participate in the study. Two stratifications will be made for each block. The first stratification will be by the type of professional involved and divided into three categories: physicians, health professionals (nurse, midwife, nutritionist, physical therapist, dentist, paramedic, pharmacist, podiatrist), and psychosocial professionals (psychologists and social workers). The second stratification will be by the work sector of each healthcare center. In each stratum, a similar number of people will be randomized for the experimental and control group using the software package “blockrand,” which creates randomizations for block random clinical trials.

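### Randomisation is stratified by type of professional and work sector, but neither outcome model includes them and the scale-specific ANCOVAs also drop previous contact: a small, avoidable loss of precision

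*Protocol article*

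**What the plan says.** Under Design, centres serve as blocks and two stratifications are made within each: "The first stratification will be by the type of professional involved and divided into three categories" (physicians, health professionals, psychosocial professionals), and "The second stratification will be by the work sector of each healthcare center". Allocation is meant to be close to equal between the two arms within every such stratum.

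Power and Data Analyses names the terms of two analyses:

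- **MANCOVA (overall test):** centre is a factor, "while the pre-test measurement and previous contact with someone with SMD are considered as co-variables".
- **Mixed ANCOVA (each scale, once the overall test has succeeded):** group as a fixed factor, pre-measurement as a covariate, centre as a random factor.

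The Introduction gives grounds for expecting both omitted variables to be prognostic. On profession, it reports that "professionals closest to the area of social sciences, such as psychologists, would have less stigma" than physicians and nurses, although the sentence just before describes stigma as much the same across professional groups, with some apparent differences. On contact, it cites a Chilean study in which "those who had greater contact with people with SMD had less authoritarian and restrictive attitudes".

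**The concern.** When allocation is balanced on a prognostic factor, that factor contributes little to the difference between arms. If the model omits it, its variance stays in the residual, so the reported standard error is larger than the actual sampling variation of the estimate. The trial pays for the balance and does not collect the benefit.

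Here the article is not silent on covariates. It gives a list for each model, and the lists leave out both within-centre stratification factors. They also differ from each other: previous contact was thought worth adjusting for in the overall test but is absent from the tests that give the result for each scale. No reason is given for either choice.

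At stake are some precision, the small imbalances that very small strata leave behind, and the coherence of a two-step analysis in which the second step follows from the first.

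**Working it through.** **1. Terms side by side**

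| Variable | Role at allocation | MANCOVA | Mixed ANCOVA |
|---|---|---|---|
| Centre | block | factor | random factor |
| Type of professional | stratum | absent | absent |
| Work sector | stratum | absent | absent |
| Pre-test score | none | covariate | covariate |
| Previous contact | none | covariate | absent |

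**2. The plan's own sample size.** Inputs from Power and Data Analyses: d = 0.5, power 95%, alpha 5% (taken as two-sided). With the SD set to 1:

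n per group = 2 × (1.960 + 1.645)² / 0.5² = 104 by the normal approximation. The exact noncentral t gives 105 (power 0.9501).

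The stated 105 is reproduced by a plain two-group comparison with no credit for covariates, so it does not depend on the omitted terms.

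**3. What profession can add beyond the pre-test.** The article gives no variance explained, so these inputs are assumptions. Let profession explain a share R of the variance at each visit, and let ρ be the pre/post correlation. Then:

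- variance of post given pre: 1 − ρ²
- variance of post given pre and profession: (1 − R) − (ρ − R)² / (1 − R)
- partial R² = 1 − (second / first)

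For R = 0.10 and ρ = 0.4: first = 0.84; second = 0.90 − 0.09/0.90 = 0.80; partial R² = 1 − 0.80/0.84 = 0.048.

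For R = 0.05 and ρ = 0.7: first = 0.51; second = 0.95 − 0.4225/0.95 = 0.5053; partial R² = 0.009.

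So R of 5% to 10% with ρ of 0.4 to 0.7 gives a partial R² of about 0.01 to 0.05. The pre-test has already absorbed most of the profession difference.

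**4. Effect on the standard error and on power.** SE ratio (adjusted / unadjusted) = √(1 − partial R²). Power is by the normal approximation at 105 per group, with SD 1 before adjustment.

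| Partial R² (assumed) | SE ratio | SE reduction | n per group for 95% | Power, d = 0.5 | Power, d = 0.3 |
|---|---|---|---|---|---|
| 0 | 1.000 | – | 104 | 0.952 | 0.585 |
| 0.01 | 0.995 | 0.5% | 103 | 0.954 | 0.589 |
| 0.02 | 0.990 | 1.0% | 102 | 0.955 | 0.593 |
| 0.05 | 0.975 | 2.5% | 99 | 0.961 | 0.607 |
| 0.10 | 0.949 | 5.1% | 94 | 0.969 | 0.630 |
| 0.15 | 0.922 | 7.8% | 89 | 0.976 | 0.655 |

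The rows to 0.05 are the plausible range for profession alone. The last two would need a substantial further contribution from contact, and so could apply only to the ANCOVAs.

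**5. Simulation.** Setting: 11 centres, 210 participants, allocation stratified by profession within centre, ρ = 0.5, assumed profession shares of 15/60/25%, 4,000 trials per setting. Centre was fitted as fixed effects, and work sector was not simulated.

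| R | Mean SE, omitted / included (null) | Actual SD of estimate, omitted / included (null) | Null rejection, omitted | Power at d = 0.3, omitted / included |
|---|---|---|---|---|
| 5% | 0.1198 / 0.1188 | 0.1202 / 0.1202 | 0.051 | 0.706 / 0.712 |
| 10% | 0.1197 / 0.1176 | 0.1176 / 0.1172 | 0.051 | 0.693 / 0.709 |
| 20% | 0.1200 / 0.1150 | 0.1166 / 0.1150 | 0.047 | 0.713 / 0.744 |

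Omitting profession hardly changes the actual spread of the estimate, because stratification has already balanced it. It mainly inflates the reported SE, by 0.8%, 1.8% and 4.3% in the three settings. Power at d = 0.3 is higher here than in step 4 because these models take credit for the pre-test.

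**The case against.** The strongest case against the point is that it is too small to matter. The pre-test is in both models, stratification supplies the balance, the Introduction hedges the link between profession and stigma, and at the planned d = 0.5 power moves by about one point or less for profession alone. All of that stands, and it sets the size of the finding. It does not explain why the variables used for allocation are left out when including them costs almost nothing.

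A second objection is that an article may leave stratification factors to a SAP. That would carry weight had the article said nothing about covariates, but it lists the terms of each model and the lists disagree.

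Three stronger readings are tempting, and the document does not support them:

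- **That the two steps estimate different effects because their covariates differ.** With linear models under randomisation, adding or dropping a pre-randomisation covariate leaves the average treatment effect being estimated unchanged. Only the precision and the realised estimate move.
- **That the omission biases the result or undermines the error rate or sample size.** Null rejection with profession omitted was 0.047 to 0.051, and 105 per group takes no credit for covariates.
- **That the loss equals 3% to 10% of the sample, or 6 to 21 of 210 participants.** That pools profession with contact, which the MANCOVA already includes, and its upper end makes too little allowance for what the pre-test absorbs.

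Nor can work sector be excused on the ground that centre is in the model. Sectors are strata inside a centre, and a centre term does not capture differences between them.

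**Conclusion.** The point holds as a minor one about efficiency and consistency. Both within-centre stratification factors are missing from both models, and previous contact is missing from the scale-specific ANCOVAs. The consequence is a model SE about 0.5% to 2.5% too large if profession's partial R² beyond the pre-test is 0.01 to 0.05, and somewhat more in the ANCOVAs if contact adds to it. The direction is conservative. These figures rest on assumed values for the variance explained and the pre/post correlation, since the article gives neither. Nothing here can be quantified for work sector, because neither the number of sectors nor their relation to stigma is stated.

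It is worth correcting because it is nearly free and because it must be done before outcome data are seen. Covariates added later would invite a charge of selective adjustment.

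**What to change.** 1. Add professional category (three levels, fixed effect, two degrees of freedom) to the MANCOVA and to every scale-specific mixed ANCOVA.
2. Carry previous contact into the mixed ANCOVAs, so that both steps use the same adjustment set. State its coding and that it is recorded before randomisation. Table 1 shows only a sociodemographic file at T1 and does not name contact, and the programme itself provides contact, so a later record could be affected by treatment. If it is one score or a yes/no item, it costs one degree of freedom.
3. State how work sector is handled, and do so consistently: for example, as a random effect nested in centre in the ANCOVAs where the strata allow. Centres have 18 to 40 participants, so a professional category averages only 6 to 13 people per centre (18/3 and 40/3) before the split by sector. If sector is left out for sparsity, say so and give the reason.

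For items 1 and 2 the cost is a sentence or two in the analysis section and about three degrees of freedom out of 210 participants. Professional category must be known for allocation, and contact is already a planned covariate. The cost of item 3 depends on the number of sectors, which the article does not give.

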## Discussion

It is expected that an intervention program that recognizes the aforementioned aspects will reduce the stigmatization that healthcare workers have toward people with SMD. Reducing stigma toward people with SMD should be one of the priorities of a policy aimed at ensuring the rights of people with psychiatric diagnoses and guaranteeing equity in health care. The results of this study could help future research to evaluate the potential of the program to be part of a global strategy geared toward improving equity in health care and the quality of life of people with SMD and their families.

One limitation of this study is the risk of contamination between the control and experimental groups within each healthcare center. However, it was estimated that this risk was lower given the characteristics of the centers and the program, which assumes that attitudinal change is not easily achieved and that direct contact with people having SMD is decisive. This experience cannot be transmitted to other people without a substantial effort. Therefore, considering the working conditions of the healthcare personnel (high demand and overload), group crosstalk is not expected to frequently occur, thereby decreasing the possibility of contamination. Furthermore, the study design of this intervention program avoids the methodological difficulties of clustered designs, which are the preferred choice to have less risk of contamination. The results of this study will be published in scientific journals and scientific meetings, and it will also be presented to the general public, especially to those involved in protecting the rights of people with SMD, and to health authorities. The data of this study will be available to those who request it.

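### The outcome model has only a centre effect common to both arms, so it cannot carry the correlation that group delivery creates in the intervention arm alone, and the test of the program exceeds its 5% level if that correlation is positive

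*Protocol article*

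**What the plan says.** All references are to the protocol article.

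- **Allocation.** Under Design, randomization is individual, with each centre as a block. Under Procedure, a centre needs at least 18 enrolled workers, and "The randomization process will form groups with 9 to 20 people".
- **Delivery.** Under Characteristics and Methods of the Program, health personnel attend six weekly two-hour sessions run by a health professional and a person with a diagnosis. The sessions rely on group discussion and role play. According to the end of Procedure, controls get the program only after the post-test and follow-up evaluations.
- **Analysis.** Under Power and Data Analyses, the overall test is a MANCOVA in which clustering by centre enters as a factor. If it shows success, each outcome is analysed by mixed ANCOVA with arm as a fixed factor, "pre-measurement as a co-variable, and enrollment in the primary healthcare center as a random factor". No session-group or arm-by-centre term is named for either model.
- **Sample size.** The target is stated as "To detect a moderate effect for the intervention (*d* = 0.5") "with a power of 95% and a level of significance of 5"%, giving "a minimum sample of 105 participants per group is estimated (210 participants in total"). On its origin: "This number was obtained by performing a simulation procedure using a mixed ANOVA". No ICC, centre variance or pre-post correlation is reported. "Considering a 10% loss in percentage, 231 is the minimum estimated number of participants".
- **Clustering.** The Discussion says that "the study design of this intervention program avoids the methodological difficulties of clustered designs".

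**The concern.** Individual randomization makes workers independent at entry, but it does not keep them so once one arm is treated in groups. Those who share facilitators, discussions and role plays will tend to shift together, and the article presents group reflection as part of how the program works. Controls in the same centre share no such sessions. The result is a partially nested design, with clustering by session group in one arm only.

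The stated mixed ANCOVA allows for differences between centres that affect both arms alike. It does not allow the program's effect to vary from group to group. That variation is then averaged as if it came from some 105 independent people rather than about 11 groups. Confidence intervals would be too narrow, and an ineffective program would be declared effective more than 5% of the time. This applies at post-test and at follow-up, because controls are still waiting at both.

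**Working it through.** **Inputs from the article.** d = 0.5; power 95%; significance level 5%; 105 per arm; at least 11 centres. At the minimum of 11 centres, group size is m = 210/11/2 = about 9.5 per arm per centre.

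**Assumptions, not in the article.** Session-group ICC of 0.02, 0.05 or 0.10, taken on the outcome after baseline adjustment; pre-post correlation r of 0 or 0.5; one session group per centre; outcome SD of 1.

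**1. The plan's own figure.** An unclustered two-sided two-sample t-test at d = 0.5 needs 104.93 per arm, rounded up to 105. Power is 95.01% at 105 and 94.83% at 104. A change-score test of the time-by-group interaction needs about the same number when r = 0.5: by normal approximation 8 × (1.96 + 1.645)² × 2(1 − r) = 104 per arm. The stated figure is therefore reproduced, and neither route contains an allowance for group delivery.

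**2. Why the centre term does not help.** Write the intervention mean in centre j as c_j + effect + g_j + error, and the control mean as c_j + error. In the difference, c_j cancels and the session-group effect g_j remains. The random centre intercept models c_j only.

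**3. Variance of the arm effect.**

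- Correct: V = (1 − r²) × [(1 − ICC)/105 + 1/105 + ICC/11].
- Assumed by the stated model: between (1 − r²) × [(1 − ICC)/105 + 1/105] and (1 − r²) × 2/105, depending on how much group variance leaks into the residual.

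Example at ICC 0.05, r = 0: V = 0.95/105 + 1/105 + 0.05/11 = 0.02312. The model assumes 0.01857 to 0.01905, a ratio of 1.24 to 1.21.

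**4. Type I error.** This is 2 × [1 − Φ(1.96/√ratio)].

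| ICC | Variance ratio | Type I error, formula | Type I error, simulation |
|---|---|---|---|
| 0.02 | 1.09-1.10 | 6.0-6.1% | 5.5-6.3% |
| 0.05 | 1.21-1.24 | 7.5-7.9% | 7.5-7.7% |
| 0.10 | 1.43-1.50 | 10.1-11.0% | 10.6% |

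The factor (1 − r²) cancels from the ratio, so baseline adjustment does not cure the inflation. For groups of 20, the upper size under Procedure, the formula with 2/105 in the denominator becomes 1 + 19 × ICC/2. It gives 10.7% at ICC 0.05 and 16.0% at 0.10.

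**5. Power of a valid analysis at d = 0.5.** Noncentral t with noncentrality 0.5/√V. A random treatment slope over 11 centres has 10 degrees of freedom. For the partially nested model, the Satterthwaite approximation is V²/(V_T²/10 + V_C²/104), where V_T and V_C are the two arms' contributions. It gives about 32, 28 and 23 degrees of freedom at ICC 0.02, 0.05 and 0.10.

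| ICC | r = 0, Satterthwaite | r = 0, 10 df | r = 0.5, Satterthwaite | r = 0.5, 10 df |
|---|---|---|---|---|
| 0.02 | 92% | 88% | 97% | 95% |
| 0.05 | 89% | 84% | 96% | 93% |
| 0.10 | 83% | 78% | 92% | 88% |

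At ICC 0 and r = 0, the 10-df test already has only 90.3%. Part of the drop in the 10-df columns is therefore the price of few degrees of freedom, not of group delivery.

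**The case against.** Several stronger readings are tempting, and the article does not support them.

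- **That 95% power is not delivered.** The planned ANCOVA adjusts for the pre-measurement, so r = 0 is not the planned analysis. At r = 0.5 the partially nested model keeps at least 95% power up to ICC 0.05. Neither r nor the ICC is given, so a shortfall is possible but not established.
- **That 105 is simply the independent t-test number.** The match is exact, but the article attributes the figure to a mixed-ANOVA simulation with unreported inputs, and step 1 shows another route to the same number. A condensed article may well leave such inputs to the full protocol. All that can be said is that no allowance for group delivery is visible.
- **That there is one session group per centre.** This is inferred from the 9-20 group size and is not stated. If a centre ran several groups, the same problem would arise at session-group level with smaller m.
- **That the MANCOVA certainly has the same defect.** It is described only as having centre as a factor. An arm-by-centre term is neither stated nor excluded.
- **That the Discussion sentence is false.** In context it concerns cluster-randomized designs as a way to limit contamination, and this trial does avoid those. It needs clarifying, not deleting.

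It is also fair to say that the inflation depends on an ICC nobody has reported, and that at 0.02 it is small. The directors' meetings act at centre level, and whatever reaches both arms is absorbed by the centre term.

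None of this touches the core. The per-outcome model is written out in the article, group delivery occurs in one arm only, and a shared centre effect cannot represent it.

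**Conclusion.** The point holds for the analysis model. The per-outcome mixed ANCOVA as stated understates the standard error of the arm effect for any positive session-group ICC, and the MANCOVA as described shows no provision for it either. Since success on the MANCOVA opens the outcome-specific analyses, the overall test matters as much as those that follow.

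The size is a range: a nominal 5% test runs at about 6% to 11% for ICCs of 0.02 to 0.10 with 11 centres and about 9.5 workers per arm per centre, and higher with larger groups. It rests on an assumed ICC and on one group per centre.

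For power the conclusion is weaker. The 95% is not shown to be wrong. It is not supported either, because the two quantities that decide it, the session-group ICC and the pre-post correlation, are not given.

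**What to change.** 1. In each outcome model, add either a random centre-by-arm term or a session-group random effect in the intervention arm, with Satterthwaite or Kenward-Roger degrees of freedom.
2. Make the overall test allow for the same clustering, since it decides whether the outcome-specific analyses proceed.
3. State how many session groups each centre runs.
4. Keep the sample size. Restate the power from a simulation of the revised model, and report the assumed ICC and pre-post correlation.
5. In the Discussion, say that individual randomization avoids cluster randomization but not the clustering that comes from group delivery.

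The cost is changed wording, a re-run simulation, slightly wider intervals and possibly a less favourable stated power. No further participants are needed.
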